## **SUMMIT activity design and methodology**

*Outcomes:* The SUMMIT activity is a controlled trial designed to assess the relative impact of a prenatal multi-micronutrient tablet in comparison to the current MOH iron/folate tablet on frequency of maternal mortality as assessed by both the maternal mortality ratio (MMR), defined as maternal deaths per 100,000 live births, and the maternal mortality rate (MMRT), defined as the death of a woman while pregnant or within 42 days of termination of pregnancy from any cause aggravated or related to the pregnancy, expressed per 100,000 pregnancies. Two additional main outcomes of the SUMMIT activity are proportion of low birth weight infants, and infant mortality, including neonatal mortality. Secondary outcomes to be assessed include maternal morbidity, neonatal development, and nutritional status during pregnancy and lactation. In addition to examining the effect of multi-nutrients, we will document the effect of education and social marketing of the SUMMIT activity by comparing outcome rates in the iron/folate arm of the intervention area to corresponding rates in designated villages where standard prenatal care practice will continue. In a 20% subsample of pregnancies biochemical status for micronutrients, including, iron, zinc, and vitamin A, will be determined.

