*Supplementation:* Pregnant women will be provided with either an iron and folate tablet or another multi-micronutrient tablet containing iron, folate, vitamins A, B1, B2, B6, B12, C, D, and E, along with niacin, zinc, copper, selenium, and iodine. Supplements will be provided by existing MOH midwives, and be distributed from the first antenatal consultation for a confirmed pregnancy until three months postpartum. The midwives will distribute the supplements monthly as 30-tablet sachets, as is current MOH practice, and monitor the health impact through routine prenatal care visits and compliance checks. Additional compliance monitoring will be conducted by HKI field workers through spot-checking of pill counts and biochemical indices.

*Monitoring:* In addition to the distribution of supplements, midwives will continue to record the results of routine prenatal examinations, attend deliveries and record data on labor and delivery, birth weight, and APGAR scores of neonates. All of these activities are currently part of the normal maternal care protocol implemented by the MOH. The implementation of these activities will be strengthened in all villages by training and community promotion. HKI field workers will collect additional data at enrollment, at 36 weeks of gestation, and at 12 weeks postpartum on socio-economic status, food intake, and anthropometry. Deaths will be detected through the longitudinal surveillance of participants and also through the quarterly island-wide demographic surveillance system. The dual surveillance will allow the trial to document all maternal deaths (up to and exceeding 12 weeks postpartum), to allow evaluation of MMR and MMRT, and all infant deaths occurring beyond the 12-week visit. Lastly, it will allow monitoring of mortality in the non-intervention villages. For all maternal and infant deaths verbal post-mortem assessments will be made to determine the associated causes and conditions.

*Implementation schedule:* The trial will be carried out over five years in 3 distinct stages broadly scheduled as follows; Phase I- Preparation and training from December 1999-August 2000, Phase II-Supplementation and follow-up from September 2000-September 2003, and Phase III-Analysis and report preparation from October 2003-October 2004.

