## 2. *Design and Methods*

The proposed SUMMIT activity is a double blind, community-based, cluster-randomized, controlled intervention designed to assess the relative impact of multi-micronutrient supplements compared to iron/folate supplements on maternal mortality, infant mortality and low birth weight. Pregnant women will be randomized to one of approximately 300 clusters defined by the geographic area serviced by a trained midwife. This means that all women attended by a particular midwife will receive the same type of supplement. Clustered randomization was chosen due to the logistical and scientific difficulties associated with individual randomization in large scale longitudinal trials. Pregnant woman will be provided with either a daily multi-micronutrient supplement containing iron, folate, vitamin A, and zinc, along with additional B vitamins, minerals, anti-oxidants (for precise composition, see Appendix 3a), or an identical-looking daily supplement containing 30 mg iron and 400 µg folate. There will be no blank placebo group because iron/folate supplementation distribution to pregnant women is the current policy of the GOI.

The intervention will be preceded by a 6-month baseline demographic surveillance period to estimate area-specific maternal and infant mortality rates. Supplementation will then be phased in step-wise by implementation in 1/3 of the villages over 3 successive 3-month intervals. Women who refuse to be included in the trial and those in the pre-intervention areas will receive the standard GOI iron/folate tablets. The GOI iron/folate tablets will, therefore, not be withdrawn from the island but will only be used for individuals not enrolled in the intervention portion of the activity.

Supplements will be provided free to all women with a confirmed pregnancy, from the first antenatal consultation up to three months postpartum. As a joint activity between HKI and the GOI, the existing government system will distribute the supplements to pregnant women and the government-trained midwives will be involved in monitoring the health impact. HKI project staff will also encourage the midwives to provide maximum supplementation coverage. Additional non-invasive surveillance will be carried out by HKI project staff to allow adequate assessment of compliance and health impact.

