| Detectable
reduction
(%) | Total live births (LB) needed |                        |                      |
|-----------------------------------------|--------------------------------------|------------------------|----------------------|
|                                         | NMR=46/1000 LB                | PNMR=64/1000 LB | LBW=15/100 LB |
| 10                                      | 83,012                               | 58,613                 | 22,862               |
| 15                                      | 36,231                               | 25,597                 | 10,016               |
| 20                                      | 20,006                               | 14,142                 | 5,552                |
| 25                                      | 12,561                               | 8,899                  | 3,498                |

As is general practice for community-based trials, a Data Safety and Monitoring Committee will be convened, and trial data will be evaluated after two years. Should documentable reductions be likely, the committee will decide whether the trial should be terminated or extended. For example, if a 20% reduction in MMR is observed in the multi-nutrient group compared to a MMR of 600/100,000 live births in the iron/folate arm, an approximate 6-month extension would be needed to demonstrate statistical significance.

Sample size determinations are needed for the evaluation of the impact of activities, such as promotion of prenatal care and nutrition, accompanying the supplement distribution. Through the baseline demographic surveillance and continued monitoring of maternal and infant mortality as the intervention is phased in, we propose to document the effect of the activities associated with program implementation on maternal and infant mortality. This will be estimated by comparing MMR, MMRT, and IMR between the non-intervention areas and the iron/folate arm of the intervention area. For the non-intervention area we estimate that maternal and infant mortality rates will be estimated for 54,000 pregnancies. This will be compared to the rate obtained for the iron/folate arm of the intervention for 63,000 pregnancies. This will enable detection of at least a 20-25% (power=80% with  $p<0.05$ ) effect of the program implementation, independent of the multi-micronutrient impact.

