## *5. Enrollment of pregnancies*

At the onset of the supplement distribution period, pregnant women reporting to a midwife or a midwife's assistant will be enrolled into the intervention if informed consent is given. When reported to the assistant, the woman will be referred to see the midwife as soon as possible. At the time of the first visit to the midwife, the pregnancy will be confirmed by means of a urine test, or physical examination, depending on the estimated gestational age. Based on existing midwife records, we anticipate that pregnancies will be reported between 3-5 months of gestation. Reporting may be earlier once the community knows about the urine test to confirm pregnancy and about the distribution of the supplements.

Because the trial relies exclusively on pregnant women actively seeking antenatal care from the village midwife, improved midwife-seeking behavior will be important. Before the start of the trial, the midwives will be motivated to recruit three to six women in their village to assist the midwife in her trial-related tasks. The role of these assistants is to facilitate identification and enrollment of pregnant women, distribute supplements, and report complications of delivery and maternal death to the midwife. A campaign to encourage early first visits to the midwives will also be conducted in the start-up phase of the trial. The purpose of this social marketing activity is to promote early first visits, promote the use of supplements and to promote the services of the village midwife and her assistants.

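### The programme-effect contrast is mainly a before/after comparison, and its two sides are not tied to one population or one source of deaths

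*Protocol*

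**What the plan says.** The protocol's Sample Size section (VIII.B.3) defines the contrast: "This will be estimated by comparing MMR, MMRT, and IMR between the non-intervention areas and the iron/folate arm of the intervention area". It gives the two sizes as "For the non-intervention area we estimate that maternal and infant mortality rates will be estimated for 54,000 pregnancies" and "This will be compared to the rate obtained for the iron/folate arm of the intervention for 63,000 pregnancies". It claims 80% power for a 20-25% effect of programme implementation, separate from any effect of the multi-micronutrient tablet. For the same contrast, the Sample Size paragraph of the Executive Summary gives at least 25% for MMR.

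The comparator is described in several ways:

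- Executive Summary, Outcomes: "designated villages where standard prenatal care practice will continue".
- Executive Summary, Sample Size: data gathered in the phase-in period before enrolment.
- VIII.B.2 Design and Methods: "Supplementation will then be phased in step-wise by implementation in 1/3 of the villages over 3 successive 3-month intervals", after a six-month baseline; areas awaiting their turn keep the standard government tablet.
- VIII.B.8 Data collection: baseline ratios against the iron/folate group.
- VIII.B.12 Data management and analysis: pre- against post-intervention areas for the iron/folate arm.

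On who enters the arm, VIII.B.5 says "Because the trial relies exclusively on pregnant women actively seeking antenatal care from the village midwife", with consent required and reporting expected at 3-5 months. The surveillance in VIII.B.4 covers all pregnant women and women of childbearing age. On deaths, the Monitoring paragraph says "Deaths will be detected through the longitudinal surveillance of participants and also through the quarterly island-wide demographic surveillance system".

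**The concern.** A programme effect can be read from this contrast only if its two sides would have had the same death rate without the programme. Three features threaten that.

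- **Time.** Most of the comparator is earlier and spans one half-year, while the Executive Summary wants at least two years of enrolment to cover the seasons.
- **Population.** Women who seek out a midwife, consent and reach 3-5 months of pregnancy may differ in risk from all pregnant women. Deaths and losses before entry cannot be counted among them.
- **Detection.** Participants are followed individually as well as through the quarterly surveillance.

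The Executive Summary ranks this question as equally important, and section V makes it the basis of cost-benefit advice to government. A biased estimate could therefore steer budgets.

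**Working it through.** **1. Reproduce 54,000 and 63,000.** Inputs: 72,000 pregnancies a year (VIII.B.1), that is 6,000 a month; a 6-month baseline (VIII.B.4); one third of villages starting every 3 months (VIII.B.2); 2 years of recruitment (VIII.B.3).

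- Baseline: 6 × 6,000 = 36,000.
- Awaiting roll-out, months 0-3: 2/3 × 18,000 = 12,000.
- Awaiting roll-out, months 3-6: 1/3 × 18,000 = 6,000.
- Comparator: 36,000 + 12,000 + 6,000 = **54,000**, as stated.
- Enrolment: 24 × 6,000 − 18,000 = **126,000**; half is **63,000**, as stated.

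So 36,000/54,000 = 67% of the comparator precedes all supplementation. The 18,000 concurrent pregnancies face (6,000 + 12,000)/2 = 9,000 iron/folate pregnancies in the same six months.

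**2. Gap in calendar time** (months from the start of supplementation).

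- Comparator mean: (36 × (−3) + 12 × 1.5 + 6 × 4.5)/54 = −1.2.
- Enrolled mean: (6 × 1.5 + 12 × 4.5 + 108 × 15)/126 = 13.4.
- Gap: about 14.5 months.

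**3. Detectable reduction in MMR.** Two proportions, two-sided 5%, 80% power. With n1 comparator and n2 = k·n1 iron/folate pregnancies, solve

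n1 = [1.96·√((1+1/k)·p̄(1−p̄)) + 0.84·√(p1(1−p1) + p2(1−p2)/k)]² / (p1−p2)²

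for p2. The effective n is pregnancies × 0.90 (10% loss) × 0.85 (non-live births) / 1.2 (clustering), a factor of 0.6375; the three allowances come from VIII.B.3. As a check on method, with continuity correction and factors 1.2 × 1.1/0.85 the formula gives about 119,840 for a 30% reduction at MMR 400, against 119,865 in the protocol's table.

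| Comparison | MMR 400 | MMR 600 | MMR 800 |
|---|---|---|---|
| 54,000 v 63,000 | 29.9% | 24.7% | 21.6% |
| 18,000 v 63,000 | 40% | 34% | 30% |
| 18,000 v 9,000 | 61% | 51% | 45% |
| 18,000 v 9,000, continuity corrected | 64% | 53% | 47% |

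The stated 20-25% thus holds at MMR 600-800 with all 54,000. At the protocol's conservative MMR of 400 it is about 30%.

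**4. Size of possible bias with no true effect.** The inputs here are assumptions; the documents give none of them.

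- Selection: a share q never enrols and has RR times the risk. Apparent reduction = 1 − 1/[(1−q) + q·RR]. For q = 0.2, RR = 2: 1 − 1/1.2 = 17%. Range for q = 0.1-0.2 and RR = 1.5-3: 5-29%.
- Detection: the comparator misses a share m of deaths found among participants. Apparent increase = 1/(1−m) − 1, which is 11% for m = 0.1 and 25% for m = 0.2. At m = 0.2 a true 25% reduction would look like 1 − 0.75/0.8 = 6%.
- Secular decline of 2-5% a year over 14.5 months: apparent reduction of 2-6%.

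These act in opposite directions, so the sign of the net bias is not known.

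**The case against.** The strongest reply is that VIII.B.3 describes the contrast by area and introduces it with the baseline surveillance and the continued monitoring during phase-in. The 63,000 also makes no deduction for women who do not enrol. On that reading both sides could be all pregnancies from one surveillance system, and the differences in population and detection would largely vanish. This stands as a possible reading. But 126,000 is the enrolment target, enrolment requires attendance and consent, and refusers stay on the government tablet, so an arm of enrolled women is the likelier reading. The supportable defect is that source and denominator are not fixed. Near-complete enrolment would shrink selection by attendance but not late entry.

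A reader might also infer more than the text supports:

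- **That roll-out order is non-random.** The protocol does not say how the thirds are chosen.
- **That concurrent control villages are promised.** The Executive Summary mentions villages continuing standard care but not for how long; other sections openly describe a before/after contrast. The wording needs reconciling, but no promise is broken.
- **That comparator deaths are found by quarterly surveillance alone.** Under VIII.B.8, midwives already detect maternal and neonatal deaths in routine care, and verbal autopsy is planned for all maternal and infant deaths. The latter aligns classification more than detection. Intensity may still differ.
- **That the trial's main result is compromised.** The multi-micronutrient versus iron/folate comparison is randomised and does not use these data. The programme contrast is also absent from the specific objectives.

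**Conclusion.** The concern holds in limited form. As sized, the contrast is largely before/after: two-thirds of the comparator precedes supplementation and covers a single half-year. That follows from the protocol's own figures. As most naturally read, it also sets consenting attenders against all pregnant women, with closer follow-up for deaths on one side. The net direction of bias is unknown, and any selection figure, such as 5-29%, is an assumption and not a finding.

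The 20-25% claim rests on the pre-trial data and on an MMR of about 600-800. Concurrent data alone detect about 45-64% (MMR 800 down to 400, with or without continuity correction). The result can describe the whole package only: under section IV the trial's iron/folate tablet and its distribution also differ from current practice, so education and promotion are not isolated.

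This should be fixed because the estimate is meant to inform policy. It does not threaten the randomised comparison.

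**What to change.** For this contrast only:

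1. State that numerators and denominators on both sides come from the same island-wide quarterly surveillance, counting all pregnancies and live births in the iron/folate villages whether or not the woman enrolled.
2. Allocate at random which third of villages starts first, second and third, since no method is given. This must be done before roll-out.
3. Reconcile the Executive Summary (Outcomes and Sample Size) with VIII.B.2, 3, 8 and 12 on what the comparator is. Report the result as a non-randomised, mainly before/after estimate of the whole package.
4. Report the concurrent phase-in comparison as a sensitivity analysis, stating that 18,000 against about 9,000 pregnancies detects only about 45-64% in MMR. State also that 20-25% relies on the pre-trial data and an MMR of about 600-800, and is about 30% at 400.

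No new data are needed, because the surveillance already runs throughout. The costs are slightly harder roll-out logistics and a less favourable stated precision. A primary model adjusting for calendar quarter is not asked for: it would lean mainly on the six phase-in months and so largely give up the 20-25% aim for MMR.

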*Sample Size:* The SUMMIT activity will aim to detect a reduction in both MMR and MMRT of at least 30% with a power of 80% and significance level of 0.05. Current estimates of the MMR in various districts on Lombok range from 400 to 800 maternal deaths per 100,000 live births and randomization for the trial will be by clusters consisting of geographic areas serviced by each of the 300 midwives providing prenatal care. Assuming 400 maternal deaths per 100,000 live births and a 10% loss to follow-up, the trial would require enrollment of 102,000 live birth pregnancies allocated to either an iron/folate or multinutrient supplement to detect a 30% reduction in MMR. Because not all pregnancies result in a live birth, it is estimated that the required sample size be increased an additional 15% to 120,000. This sample size will also allow detection of similar reductions in MMRT. It is proposed that enrollment be phased in over a 6-month period and continue for at least 2 years to accommodate seasonal effects. The phased in implementation along with the approximately 72,000 pregnancies occurring each year throughout the trial area yields a projected enrollment of 126,000 pregnancies. The additional margin of enrollment provides the ability to detect reductions in MMR as little as 22% if ratios approach 800 per 100,000 live births. With regard to low birth weight and infant mortality rates, the projected sample size will allow detection of at least a 10% reduction in low birth weight and infant mortality rates, including neonatal mortality rates. Equally important is determination of the impact of the social marketing and education programs that will accompany the trial implementation in the intervention area. Data concerning outcome variables in the absence of the intervention will be collected during the phase-in period prior to enrollment. This will result in the ability to detect at least a 25% difference in MMR between the iron/folate arm of the intervention area compared non-intervention areas.

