|                                         | MMR=400                                                                   | MMR=600 | MMR=800 |
| 15                                      | 509,635                                                                          | 339,137        | 253,887        |
| 20                                      | 281,023                                                                          | 187,017        | 140,012        |
| 25                                      | 176,230                                                                          | 117,290        | 87,815         |
| 30                                      | 119,865                                                                          | 79,777         | 59,731         |
| 35                                      | 86,232                                                                           | 57,381         | 42,967         |
| 40                                      | 64,581                                                                           | 43,035         | 32,192         |

Assuming a conservative MMR estimate of 400 per 100,000 live births, enrollment of 120,000 pregnancies will allow determination of a reduction in MMR of at least 30% with a power of 80% and significance level of 0.05. Similar reductions in MMRT will also be detectable because such rates are expected to be higher given that deaths prior to a live-birth delivery would be included. Given the estimated 72,000 pregnancies per year in the 300 villages on Lombok, and taking into account the phased in implementation schedule, the SUMMIT activity will plan to enroll 126,000 pregnancies over a 2 year active recruitment period. If MMR and MMRT approach 600-800 per 100,000 live births or pregnancies, which is possible considering the high rates of infant and under-five mortality, the sample size of 126,000 pregnancies will allow determination of a statistically significant reduction in MMR and also MMRT of 22-25%.

For infant mortality it will be important to also determine the age-specific effects on neonatal mortality rate (NMR, birth to 30 day mortality) and post-neonatal mortality rate

(PNMR, 1 to 12 months). The projected sample size and trial duration will allow detection of at least a 10% change in NMR and PNMR. In addition, the study will easily detect a difference of 10% in the proportion of low-birth weight (LBW) infants.

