## *12. Data management and analysis*

The first check of the forms will be performed in the field by the field supervisors. Data entry will be done using the *SPSS for Windows* program. Data will be entered in batches, and 10% of each batch will be cross-checked by data-entry supervisors. Batches for which unacceptable error rates are obtained will be re-entered and checked until acceptable

quality standards are met. The data-entry program will prohibit entry of invalid or impossible values and generate a query for follow-up. After data have been entered, additional outliers will be identified and checked against the original questionnaires. Queries regarding unclear or incomplete data will be referred to the field for appropriate follow-up. This system has been field-tested by the HKI NSS and functions well. Primary analyses will compare key outcome event rates event rates, MMR, MMRT, PNMR, and LBW in the multi-micronutrient group with the iron/folate group. However, the SUMMIT activity will not only provide information concerning the impact of micronutrients on these indicators, but it will also assess the specific impact of activities accompanying the intervention such as promotion of prenatal care and social marketing. This will be done by comparison of event rates in the pre and post-intervention areas for the iron/folate arm. This enables one to individually assess the impact of the various components of the SUMMIT activity on the key health outcomes. Relative cost-benefit analyses can therefore be carried out for the various interventions.

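### For maternal mortality ratio (MMR), the programme-effect comparison of 54,000 with 63,000 pregnancies detects about 30%, 25% and 22% at MMR 400, 600 and 800, not the stated 20-25%

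*Protocol*

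**What the plan says.** Section VIII.B.3 (Sample Size) evaluates the activities that accompany supplementation by "comparing MMR, MMRT, and IMR between the non-intervention areas and the iron/folate arm of the intervention area". For the non-intervention side, "maternal and infant mortality rates will be estimated for 54,000 pregnancies"; the other side is "the iron/folate arm of the intervention for 63,000 pregnancies". It concludes: "This will enable detection of at least a 20-25" per cent effect, with 80% power and p<0.05. No baseline MMR is attached to that range.

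The Executive Summary (SUMMIT activity design and methodology, Sample Size) gives a different figure for the same contrast and ties it to MMR: "This will result in the ability to detect at least a 25% difference in MMR between the iron/folate arm of the intervention area" and non-intervention areas. It names no baseline either.

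For the main randomised comparison, section VIII.B.3 tabulates the pregnancies needed by baseline MMR and size of reduction. It then reads the table at the low end: "Assuming a conservative MMR estimate of 400 per 100,000 live births, enrollment of 120,000 pregnancies will allow determination of a reduction in MMR"; the reduction named there is 30% or more. It credits the planned 126,000 pregnancies with 22-25% if MMR is 600-800.

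Section VIII.B.12 (Data management and analysis) describes the programme analysis as "comparison of event rates in the pre and post-intervention areas for the iron/folate arm".

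**The concern.** The programme contrast has 54,000 + 63,000 = 117,000 pregnancies, fewer than the 126,000 of the main comparison and slightly unbalanced. On the same outcome, power and significance level it cannot detect a smaller effect than the larger comparison. Yet its stated range starts at 20%, while the main comparison is given 30% at MMR 400 and 22-25% at 600-800. The same section also says that the main comparison would need about six more months to show a 20% reduction against an MMR of 600.

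The Executive Summary treats this evaluation as no less important than the supplement comparison, and section V plans cost-benefit advice to the government from it. If a reader believes that 20% is detectable when power for it is below one half at the planning MMR, a null result could wrongly count against promotion and midwife strengthening.

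**Working it through.** **Inputs (section VIII.B.3).** Group sizes 54,000 and 63,000; baseline MMR 400 to 800 per 100,000 live births; power 80%; significance level 0.05; 20% increase for clustering; about 10% loss to follow-up; 15% allowance for pregnancies without a live birth.

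**Formula.** Two-sided comparison of two proportions, with p1 the baseline rate, p2 = p1 × (1 − reduction), k = n2/n1 and p̄ = (p1 + k·p2)/(1 + k):

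n = {1.960·√[p̄(1−p̄)(1+1/k)] + 0.842·√[p1(1−p1) + p2(1−p2)/k]}² / (p1−p2)²

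Continuity correction: n′ = (n/4)·{1 + √[1 + 2(1+1/k)/(n·|p1−p2|)]}²

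Inflation to pregnancies: 1.2 × 1.1 / 0.85 = 1.5529.

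**Reproducing the MMR table.** At MMR 400 and a 30% reduction, p1 = 0.0040, p2 = 0.0028 and k = 1. Then n = 36,937 per arm, n′ = 38,586, both arms 77,171, and 77,171 × 1.5529 ≈ 119,842. The table prints 119,865. All 18 cells agree within 0.13%, so the basis of the table is known.

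**Reading the table directly.** Set the 117,000 available against the requirement:

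| Reduction | MMR 400 | MMR 600 | MMR 800 |
|---|---|---|---|
| 20% | 281,023 | 187,017 | 140,012 |
| 25% | 176,230 | 117,290 | 87,815 |
| 30% | 119,865 | 79,777 | 59,731 |

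Every entry in the 20% row exceeds 117,000. The 25% row is far out of reach at MMR 400 and only about met at 600.

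**Solving for this comparison.** Effective sizes are 54,000 / 1.5529 = 34,773 and 63,000 / 1.5529 = 40,568, with k = 63/54. Solving the formula for the reduction gives:

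| | MMR 400 | MMR 600 | MMR 800 |
|---|---|---|---|
| Detectable reduction, all factors | 30.3% | 25.0% | 21.8% |
| Same, no continuity correction | 29.7% | 24.6% | 21.5% |
| Power for a 20% reduction | 43% | 59% | 72% |
| Power for a 25% reduction | 62% | 80% | 90% |

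The power rows use the continuity correction; without it, power at MMR 400 is 45% for 20% and 64% for 25%. A 20% reduction becomes detectable only at an MMR of about 959, above the planning range and above the upper estimate of 8.9 per 1,000 in Table 1.

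**Other settings (with continuity correction).**

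| | 400 | 600 | 800 |
|---|---|---|---|
| No inflation at all | 24.7% | 20.3% | 17.7% |
| Clustering factor dropped, others kept | 27.9% | 23.0% | 20.0% |
| Maternal mortality rate per pregnancy (MMRT): live-birth factor dropped, others kept | 28.1% | 23.2% | 20.2% |

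For infant mortality at 110.5 per 1,000 (Table 1), with all factors, about 6% is detectable.

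**The case against.** **No baseline is stated.** The range for 126,000 pregnancies is quoted at MMR 600-800, and 20-25% may follow the same convention. The table's answer there is about 22-25%, so the error would be some two points at one end. This is fair: the upper part of the range is attainable from MMR 600. It does not rescue the 20% end, nor the Executive Summary's unqualified 25% at the MMR of 400 that the protocol itself calls conservative.

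**The table may be the wrong yardstick.** It was built for the randomised two-arm design. The programme contrast is not randomised, and its comparator is followed by demographic surveillance, so the true clustering and loss factors could be smaller or larger. That stands as a caution. But the protocol gives no reason to drop any factor: both groups are counted in pregnancies, the villages are still clusters, and 63,000 is half of the enrolled 126,000.

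**The sentence covers three outcomes.** This stands. For infant mortality, 20% is easily detectable. For MMRT, which is counted per pregnancy, the result is about 28% / 23% / 20%, which lies in the stated range at 600-800 but not at 400.

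**Stronger readings that the document does not support.** A reader might infer that 20-25% can arise only if every adjustment was left out. Dropping all of them does give about 25% and 20% at MMR 400 and 600, but dropping only the clustering factor gives 23% and 20% at 600 and 800, so the origin of the figure cannot be established. A reader might also take section VIII.B.12 to confine the comparator to iron/folate villages, roughly halving the 54,000. That wording is loose and can equally mean pre-intervention areas against the iron/folate arm. Section VIII.B.3 gives 54,000, section VIII.B.8 compares baseline with the iron/folate group without that restriction, and no halved figure appears anywhere. It calls for clarification, not for a recalculated power.

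**Conclusion.** The stated detectable effect is wrong for MMR on the protocol's own assumptions. The comparison detects about 30% at MMR 400, 25% at 600 and 22% at 800. Within 400-800 it never reaches 20%, and it reaches 25% only from about MMR 600. The gap is some 5 to 10 percentage points at the planning MMR of 400 and about 2 points at the lower end if MMR is 800.

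This rests on a two-sided test at 0.05, 80% power and the three inflation factors carried over from the main table. The last is an assumption for a non-randomised contrast, though the only one that the protocol offers. The finding does not extend to infant mortality, and the size and power of the randomised comparison do not depend on it.

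**What to change.** In section VIII.B.3 and in the Executive Summary:

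- Replace the 20-25% and 25% figures with about 30% / 25% / 22% for MMR at baseline 400 / 600 / 800.
- Name the baseline, the sidedness and the clustering, loss and live-birth factors. If different factors are meant for this contrast, state and justify them, and recompute.
- Give infant mortality its own statement. If MMRT is quoted, give about 28% / 23% / 20%, noting that the live-birth factor does not apply.
- Reword the comparator in section VIII.B.12 so that it agrees with the 54,000 pregnancies in section VIII.B.3.

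The cost is protocol wording only. Enrolment, design and schedule do not change, but the stated sensitivity of the programme evaluation becomes less favourable.
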